#### Management practices

baseline information was collected on management practices through a survey of five-point Likert scale questions related to seven management dimensions. In total, the tool contained 82 questions. Better practices were associated with higher scores. This questionnaire consisted of different facets of the management process including: workplace organization, financial management, personnel management, supervision, transparency, accountability and community involvement. For each section of the questionnaire, one score was calculated by summing each of the values of selected options, which ranged from 0 to 5. The overall management score was then calculated as the mean score of the different management facets. In the future, the same questionnaire will be applied in two points during the implementation of the intervention—one in month six and at the end of the implementation in month 12.

### Participant timeline

All details about the project timeline and duration of the intervention are depicted in Fig. 4.

**Fig. 4 Fig4:**
[figure not shown]
Study design and timeline

### Sample size

Since we had a fixed number of sites (n = 32), we ran power calculations to examine the varying amounts of power that were achievable, given a variety of effect differences between treatment and control groups. The point estimate for log cost per client tested positive and accompanying standard error used in the calculations are based on data from a relevant previous costing study (ORPHEA: Assessing cost and technical efficiency of HIV prevention interventions in sub-Saharan Africa) [14–16]. Given sample size and assumptions, there was 80% power to detect a 1.09 unit difference (USD) in the log cost between the treatment and control groups.

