### Outcomes

Our primary outcome of interest is service delivery efficiency, as measured by the CBO-level average cost per service delivered, which is referred to as *unit cost*. Unit cost will be calculated for three services provided by the CBOs: (1) HIV testing and counselling, (2) HIV education, and (3) syndromic management of STIs.

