### Allocation

Thirty-two sites were stratified in two strata of geographic region—north and south—with 8 sites in the north stratum and 22 sites in the south stratum. The north and south regions are climatically, linguistically and culturally distinct. More importantly, the HIV epidemic also affects the regions differently; the largest concentration of HIV/AIDS is in the south. Given that such factors are likely not independent of HIV service delivery and efficiency, stratifying the randomization by these strata improves the balance between treatment groups. Within strata, we randomly assigned sites to either treatment or control groups. Treatment status was assigned using the randomization package in STATA [17]. We specified that the package run 10,000 iterations and selected the randomization with the highest (i.e. least significant) p-values across t-tests on four key input and output indicators (clients served, referrals given, condoms distributed, and number of FSW tested). We allocated 16 sites to the treatment group and 16 to the control group. One site was later excluded because it no longer served the FSW population at the start of the trial period. The final sample included 31 sites, with 16 in the treatment group and 15 in the control group (Fig. 5). We explained to participants that they were involved in a costing study, but we never revealed whether they were part of the treatment or the control groups.

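### The only stated power figure puts a currency unit on a log difference and refers to a different outcome and comparison from the planned primary analysis

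*Protocol article*

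**What the plan says.** The Sample size section of the protocol article gives the starting point: "Since we had a fixed number of sites (n = 32), we ran power calculations to examine the varying amounts of power that were achievable". The inputs came from an earlier costing study: "The point estimate for log cost per client tested positive and accompanying standard error used in the calculations" rest on that study's data. The result is that "there was 80% power to detect a 1.09 unit difference (USD) in the log cost between the treatment and control groups". The section gives no log base, SD, significance level or sidedness, and does not express the effect as a ratio or percentage.

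Outcomes: "Our primary outcome of interest is service delivery efficiency, as measured by the CBO-level average cost per service delivered". Also: "Unit cost will be calculated for three services provided by the CBOs", namely HIV testing and counselling, HIV education, and syndromic management of STIs. The Unit cost section divides total cost per intervention by the number of clients served by that intervention. It lists the number of women tested positive among the outputs collected, but defines no unit cost with that denominator.

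Statistical methods: the dependent variable is mean cost per client served, by intervention and organisation. It is fitted by ordinary least squares with group, period and their interaction, plus covariates found imbalanced at baseline. No log transformation is stated.

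Allocation: "We allocated 16 sites to the treatment group and 16 to the control group". After one exclusion, "The final sample included 31 sites, with 16 in the treatment group and 15 in the control group".

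**The concern.** Three things in the power sentence do not fit the rest of the article.

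- **Unit.** Subtracting two logs gives the log of a ratio, and the currency cancels. The USD label invites the reader to take the detectable effect as about one dollar per client. It is a multiplicative change, and a large one if the logs are natural.
- **Outcome.** The figure is for cost per client tested positive. None of the three primary unit costs has that denominator, and it is not the dependent variable of the model.
- **Comparison.** The sentence describes a difference between groups. The planned effect is a before-after interaction, whose precision depends on how strongly an organisation's baseline and endline costs are correlated.

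This is the only power statement in the article. A reader who relies on it cannot tell how large a saving the trial could miss, and may give a non-significant result more weight against the intervention than it can bear.

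**Working it through.** **Inputs from the article.** Detectable difference 1.09 in log cost; power 80%; 32 sites, allocated 16/16; final sample 16/15.

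**Assumed, because not given.** Natural log; two-sided 5% t-test; SD of log cost back-solved; baseline-endline correlation r varied from 0 to 0.9.

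**1. Can 1.09 be reproduced?** No. Without the SD, significance level and sidedness it can only be checked for coherence.

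**2. Meaning of 1.09.** Ratio = exp(1.09) = 2.97. Reduction = 1 − exp(−1.09) = 0.664, or 66%. With base-10 logs it would be 10^1.09 = 12.3-fold, a 92% reduction. Neither converts to dollars without a baseline unit cost, which the article does not give.

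**3. Implied SD at 16/16.** Normal approximation: SD = 1.09 / [(1.960 + 0.842) × √(2/16)] = 1.09 / 0.9905 = 1.10. Noncentral t: 1.065. At one-sided 5% the values are 1.24 and 1.21. These are plausible SDs for a log cost, so 1.09 makes sense as a log difference.

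**4. Effect of losing one site.** With SD 1.065, moving from 16/16 to 16/15 lowers power at 1.09 from 80% to 78.6%. The 80% detectable difference rises from 1.09 to 1.11 (ratio 3.03, reduction 67%).

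**5. Why the outcome matters.** For testing, let C be cost, N clients tested and P clients positive. Then log(C/P) = log(C/N) − log(P/N). The two log costs differ by the log of the positivity rate, which varies between sites and may be correlated with unit cost. The SD of one is therefore not the SD of the other, and the difference can go either way. For education and STI management there is not even this link.

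**6. Illustration for a log-scale difference-in-differences at 16/15.** The SD of the change is 1.065 × √(2(1 − r)), entered in the same noncentral t calculation:

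| r | SD of change | Detectable log difference | Ratio | Reduction |
|---|---|---|---|---|
| 0 | 1.506 | 1.57 | 4.80 | 79% |
| 0.5 | 1.065 | 1.11 | 3.03 | 67% |
| 0.7 | 0.825 | 0.86 | 2.36 | 58% |
| 0.9 | 0.476 | 0.50 | 1.64 | 39% |

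The SD here comes from the wrong outcome, so it should be varied too. At r = 0.5 the detectable reduction is 41% with SD 0.5 and 73% with SD 1.25. Over SD 0.5 to 1.25 and r from 0 to 0.9 it spans 21% to 84%.

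**The case against.** The strongest defence is that this is a slip of labelling. The sentence does say the difference is in log cost. The number of sites was fixed and every eligible site was included, so the figure did not set the sample size. The Sample size section openly gives 32 sites, and Allocation explains the later exclusion. The Discussion warns that the small sample will probably give wide standard errors. An article may also leave the SD and the correlation to a fuller document.

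Much of this stands. No sample size or allocation changes, the lost site is minor, and the absence of a stated correlation is not itself a fault. But the sentence puts a wrong unit on its effect and attaches 80% power to an outcome that is not the primary one. The general remark in the Discussion corrects neither.

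Four stronger readings are tempting, and the documents do not support them:

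- *The calculation behind 1.09 is wrong.* It cannot be checked, and the implied SD is plausible.
- *It was a simple 16 versus 16 comparison.* The SD above was solved so that such a design gives 80%, so agreement proves nothing. Whether repeated measures were allowed for is unknown.
- *The trial can detect only a threefold change in its primary outcome, with about 8% power for a 20% saving or 42% for a 50% saving.* Those powers come from the same back-solved SD for the wrong outcome, in an endline-only comparison. They are illustrative.
- *Few management programmes could achieve such an effect.* The article gives no effect sizes from which to judge this.

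**Conclusion.** The power statement is wrong as written and does not describe the planned primary analysis. The unit error is certain, because no choice of log base gives a log difference a currency. The size of 2.97-fold, or 66%, rests on natural logs. The mismatch of outcome and comparison follows from setting Sample size against Outcomes, Unit cost and Statistical methods.

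The effect detectable for cost per client served is unknown from this document. The 79% to 39% range assumes a log-scale analysis, a two-sided 5% test and the back-solved SD. It shows how far the answer depends on quantities not given, and is not an estimate for the real endpoint.

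**What to change.** In the Sample size section:

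1. Delete the USD label, state the log base, and give 1.09 as a ratio and a percentage, labelled as referring to cost per client tested positive.
2. Recompute the detectable effect for each of the three unit costs per client served, at 16/15, under the planned difference-in-differences model and on the scale that model will use (log or money). Take the between-organisation SD from the baseline data already being cleaned, and state a range for the correlation between an organisation's baseline and endline unit cost.
3. State that a non-significant result does not exclude savings smaller than the recomputed figure, and that conclusions will rest on the confidence interval of the effect.

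The cost is one recalculation and a rewritten paragraph, with no change to sites or allocation and no new data collection. The stated figure may look less favourable.

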### Allocation

Thirty-two sites were stratified in two strata of geographic region—north and south—with 8 sites in the north stratum and 22 sites in the south stratum. The north and south regions are climatically, linguistically and culturally distinct. More importantly, the HIV epidemic also affects the regions differently; the largest concentration of HIV/AIDS is in the south. Given that such factors are likely not independent of HIV service delivery and efficiency, stratifying the randomization by these strata improves the balance between treatment groups. Within strata, we randomly assigned sites to either treatment or control groups. Treatment status was assigned using the randomization package in STATA [17]. We specified that the package run 10,000 iterations and selected the randomization with the highest (i.e. least significant) p-values across t-tests on four key input and output indicators (clients served, referrals given, condoms distributed, and number of FSW tested). We allocated 16 sites to the treatment group and 16 to the control group. One site was later excluded because it no longer served the FSW population at the start of the trial period. The final sample included 31 sites, with 16 in the treatment group and 15 in the control group (Fig. 5). We explained to participants that they were involved in a costing study, but we never revealed whether they were part of the treatment or the control groups.

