### Statistical methods

At the time of writing, baseline data cleaning was in process. Findings from both the baseline data and prospective data collection will be published in subsequent papers. For the purposes of baseline analysis, the data will be restricted to the 2016 fiscal year (January to December).

For the endline analysis, we will first assess baseline balance between treatment and control groups on key process and outcome measures, including inputs, outputs, costs and cost per FSW served. We will also examine descriptive statistics of the management scores. We will calculate unit costs and then measure the mean cost per client served at baseline and at endline for treatment and control groups. We will compare the two through multivariate ordinary least squares (OLS) regression analysis, using a “difference-in differences” (DiD) approach [18] to account for time-invariant differences between treatment and control groups:2$${\hbox{Y}}_{\text{ic}} = {\hbox{a}} + {\hbox{b}}_{ 1} {\hbox{x}}_{ 1} + {\hbox{b}}_{ 2} {\hbox{x}}_{2} + {\hbox{b}}_{ 3} ({\hbox{x}}_{1*} {\hbox{x}}_{2}) + [{\hbox{b}}_{4} {\hbox{x}}_{4} + \ldots {\hbox{b}}_{\text{n}} {\hbox{x}}_{\text{n}} ] + {\hbox{e}}$$where the outcome Y is the mean cost per client served for each intervention *i*, in CBO *c* x_1_ is the treatment assignment (x_1_ = 1 if treatment and x_1_ = 0 if control); x_2_ is the time point (x_2_ = 0 if before and x_2_ = 1 if after the intervention); x_4 _− x_n_ are all variables that were identified as imbalanced at baseline. Despite the rigorous randomization procedure, the small sample size and diversity in the country may still cause unobservable characteristics linked to the implementation of services—and more importantly, to efficiency—to be unbalanced between treatment and control groups. In anticipation of this possibility, using a quasi-experimental DiD approach allows any baseline differences to be “differenced out” when measuring the effect.

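### The allocation was balanced on region and four indicators, but the covariate rule will almost surely leave these out of Equation 2, so standard errors are too large by an amount the documents do not fix

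*Protocol article*

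**What the plan says.** Protocol article, Allocation. Thirty-two sites were stratified into north and south, "with 8 sites in the north stratum and 22 sites in the south stratum". Region is used because "such factors are likely not independent of HIV service delivery and efficiency". Within strata, "We specified that the package run 10,000 iterations and selected the randomization with the highest (i.e. least significant) p-values across t-tests" on four indicators: clients served, referrals, condoms handed out and FSW tested. "We allocated 16 sites to the treatment group and 16 to the control group"; one site then left because it no longer served FSW, and "The final sample included 31 sites, with 16 in the treatment group and 15 in the control group".

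Protocol article, Statistical methods. "We will compare the two through multivariate ordinary least squares (OLS) regression analysis", in difference-in-differences form. Equation 2 contains treatment (x1), time (x2) and their product, whose coefficient b3 is the effect. The remaining terms, x4 to xn, "are all variables that were identified as imbalanced at baseline". Region and the four indicators are not named as covariates. Neither the type of standard error nor a test that reflects the selection is stated. The covariate rule is fixed in this text, so it is not a detail left to a later analysis plan.

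**The concern.** The two sections pull against each other. The design forces balance on five variables, and the analysis rule admits a variable only if it is out of balance. Balance makes the effect estimate less variable to the extent that these variables predict the outcome. A model without them still counts their variance as residual noise, so the reported standard error describes a less precise trial than the one that was run. With 31 CBOs, and a Discussion that already expects wide standard errors, that lost precision matters.

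A second problem lies in how the admitted covariates enter. As main effects in a two-period model they may be unable to correct the estimate at all while still changing its standard error. A list that depends on the data could then move the p-value without moving b3.

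Third, the stated stratum sizes do not add up to the number of sites stratified, so region cannot yet be coded from the article.

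**Working it through.** **1. The plan's own figure.** The Sample size section gives 80% power for a difference of 1.09 in log cost. SD, alpha and sidedness are not stated, so the figure can only be back-solved. With two-sided 0.05 (assumed) and 16 sites per arm, SD = 1.09 / [(1.960 + 0.842) × sqrt(2/16)] = 1.10; a t-test gives 1.06. The simulation in step 4 uses 1.10 as the SD of a CBO's before-after change, which is also an assumption.

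**2. Will the balanced variables be flagged?** The selection was simulated with 10,000 stratified draws, keeping the one with the largest minimum p over four t-tests (our reading of the rule). Because 8 + 22 is not 32, strata of 10/22 and of 8/24 were both tried. The kept draw's smallest p had a median of 0.91 to 0.92, against 0.17 to 0.19 for a single stratified draw. Region is balanced by construction.

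**3. Expected size, by formula.** With one before and one after row per CBO, b3 is the difference between arms in mean change. Let R2 be the share of variance in the change explained by region and the four indicators. Under near-perfect balance:

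- unadjusted SE = 1.10 × sqrt(1/16 + 1/15) = 0.395
- true SE = 0.395 × sqrt(1 - R2)
- ratio = 1/sqrt(1 - R2) = 1.00, 1.15 and 1.41 at R2 = 0, 0.25 and 0.50
- type I error = P(|Z| > 1.96 × ratio) = 5%, 2.4% and 0.6%

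**4. Simulation.** Change-score OLS; 32 sites allocated (strata 10/22, indicators correlated 0.5), one control site dropped, 3,000 trials, nominal 5%. The adjusted model adds region and the four indicators (five terms).

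| Assumed R2 of change | SE ratio, unadjusted | Type I, unadjusted | Type I, adjusted | Power for 1.09, unadjusted | Power for 1.09, adjusted |
|---|---|---|---|---|---|
| 0 | 1.00 | 5.0% | 4.8% | 75.5% | 74.1% |
| 0.25 | 1.15 | 2.3% | 5.0% | 78.2% | 85.7% |
| 0.50 | 1.40 | 0.6% | 5.2% | 82.2% | 96.0% |
| 0.75 | 1.93 | 0.1% | 5.2% | 88.6% | about 100% |

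With strata 8/24 and uncorrelated indicators the ratios were 0.99, 1.16, 1.40 and 1.95. Other repeats under varied assumptions gave 0.96 to 1.04 at R2 = 0, 1.14 to 1.17 at 0.25 and 1.36 to 1.47 at 0.50. At R2 = 0.10 the ratio was only 1.02 to 1.06.

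**5. Main effects and b3.** Let p be the treated share. With complete pairs, the product x1·x2, after removal of the intercept, x1 and x2, is (x1 - p)(x2 - 1/2). Its two values for a CBO are -(x1 - p)/2 and +(x1 - p)/2, which sum to zero. Any covariate that takes the same value in both rows is therefore orthogonal to it, and b3 cannot change. In a constructed example with 31 CBOs and no true effect, b3 was -1.164 with and without five such covariates, while its SE went from 1.542 to 0.812. Interacting the same covariates with time moved b3 to -0.048 (SE 0.764). Only the interacted form acts on the estimate.

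**6. Strata.** 8 + 22 = 30, against 32 sites stratified. The later exclusion of one site gives 31, so it does not explain 30.

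**The case against.** A reader might infer that the trial's positive findings would be unreliable. The documents do not support that. Every calculation points the other way: intervals too wide, type I error at or below nominal, no bias. A significant result from the unadjusted model would stand.

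A reader might also infer that all the precision gained by balancing is lost. It is not: unadjusted power rises from 75.5% at R2 = 0 to 82.2% at R2 = 0.50. Only part of the gain is lost.

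The strongest objection concerns size. Differencing removes the time-constant effect of these variables on cost, so only their ability to predict the change in unit cost counts. Volume indicators may predict cost level well and change poorly. At R2 = 0.10 the distortion is a few percent, and at R2 = 0 there is none. This stands, and the size must be given as a range.

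Three further qualifications stand. The invariance of b3 needs time-constant covariates and complete pairs. Statistical methods does not say which values enter, and inputs and outputs are also collected monthly, so time-varying entry is possible and b3 would then change. But that would put post-intervention outputs, which form the denominator of unit cost, into the model. Next, a balanced indicator could still be flagged, since baseline records were collected again in August 2017 and one site left after allocation; this is unlikely. Last, the type of standard error is not named, and the figures above use a change-score model, not pooled two-row OLS.

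The stratum count may be a slip in reporting. It does not show that two sites were assigned outside the strata, and the sampling figure is not available here.

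**Conclusion.** The point holds as a conservative inefficiency of unknown size. The plan balances on region and four indicators, then applies a covariate rule that almost surely excludes them. Over an assumed R2 of 0, 0.25 and 0.50 for the change in unit cost, the standard error is about 1.0, 1.15 and 1.4 times too large, and type I error is about 5%, 2-3% and under 1%. Power for the plan's 1.09 is about 1 point higher, 8 points lower and 14 points lower than with adjustment. These figures rest on a back-solved SD, two-sided 0.05, assumed strata and the largest-minimum-p reading of the selection rule.

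Separately, if covariates are time-constant and pairs complete, the rule cannot correct b3, but it can move its p-value through a list chosen from the data. The stratum sizes are inconsistent as printed. The change is worth making before the endline analysis because it is cheap and has little downside.

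**What to change.** 1. Replace the rule based on observed imbalance with a set fixed in advance, entered where it can act. Use one row per CBO, with endline unit cost (on the log scale, if that is the analysis scale, as in Sample size) regressed on treatment, baseline unit cost, region and the four balancing indicators at their pre-randomisation values. Alternatively, keep Equation 2 and interact region and the four indicators with time; baseline cost is already an outcome row there and should not also be a regressor.
2. As a supporting check, add a randomisation test that replays the stratified best-of-10,000 selection on the 32 sites with new seeds and then removes the excluded site. First confirm that it yields enough distinct allocations. If each stratum is split in half, 8/24 strata allow C(8,4) × C(24,12) = 70 × 2,704,156, about 189 million assignments, but the selection concentrates on few of them.
3. Reconcile the stratum sizes so that they sum to the 32 sites randomised, and give the 31 analysed by region, before region is coded or the allocation replayed.

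Cost: wording and code only. The set has six terms (1 + 1 + 4), which takes residual degrees of freedom from 31 - 2 = 29 to 23. If the variables predict nothing, the loss is roughly one power point (75.5% to 74.1% with the five terms simulated). With all six terms, a separate check gave type I error of 4.4% to 5.0%.
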